#### 2.4.1 Coordination exercises (intervention group, IG)

Coordination exercises (IG) are part of ataxia-specific neurorehabilitation and focus on high repetition while allowing rather than suppressing body sway associated to ataxia (Brötz et al., 2007). Coordination exercises focus on repetitive trunk and limb movements, dynamic balance, and gait training, including training of protective movements and prevention of falling (Synofzik et al., 2013; Figure 1). The following briefly outlines the main aspects and principles of coordination exercises:

Goals and exercises in therapy should be relevant to everyday life.Fixation mechanisms, e.g., elevated shoulders, should be identified and resolved so that sway becomes visible (Brötz et al., 2007).Patients are taught how to identify and resolve fixation mechanisms over the course of therapy.Free joint mobility, especially in the upper extremity and trunk, should be achieved.Movement sequences should be challenging for coordination, rich in variation, and at the limit of performance.The training is focusing on dynamic balance.Fall training and training of protective steps are part of every therapy session.Few different exercises are trained with a high number of repetitions.

**Figure 1 F1:**
[figure not shown]
Intervention group exercise example.

Considering stroke rehabilitation in general, exercises follow the principles of motor learning, focusing on high repetition of exercises (Kwakkel et al., 2023). Bearing in mind cerebellar pathology, resulting in difficulties in motor learning (Hatakenaka et al., 2012), a high number of repetitions seems to be of special importance for patients with cerebellar lesions to compensate for difficulties in trial-and-error learning (Kelly and Shanley, 2016).

Regarding the number of repetitions and variety of exercises, a choice of 3 different exercises is recommended, each having at least 10 repetitions (per side), with a common functional goal (e.g., sit-to-stand) and their combination into one set. In a 45-min session, 3–4 sets can be performed.

Shaping is achieved by transitioning from rather static to dynamic balance exercises, from slow to fast movements (e.g., foot tapping exercises), and from single joint to complex multi-joint exercises (Ilg et al., 2009). The threshold for progressing exercises is determined by the patient's ability to resolve fixation mechanisms, with assistance from the therapist if needed. Resolving fixation mechanisms is addressed using a combination of hands-on facilitation paired with external feedback or solely through feedback, depending on the stage of motor learning. Feedback is provided by the therapist through verbal cues like “relax your shoulders” and as positive feedback on successful movements. Throughout the training, patients are guided to become aware of fixation mechanisms and learn to resolve them independently. By resolving fixation mechanisms free joint mobility is achieved. To work toward functional goals, for instance, if the objective is to ambulate from the bed to the toilette without any aid, the initial exercises may begin in a seated position and progress through activities such as sit-to-stand, standing, stepping, and eventually, walking exercises. Throughout this process, the therapist always ensures that the functional value and purpose of each exercise are clearly communicated. In order to keep the exercises challenging and at the individual performance limit until the end, i.e., when patients are already able to perform exercises on uneven ground, coordination exercises can be performed using trampolines (Giagazoglou et al., 2015). These exercises still follow the same principles.

Further details are reported according to the Template for Intervention Description and Replication (TIDieR; Hoffmann et al., 2014; Supplementary Data Sheet 1). Exercises of the IG are summarized in a handout, which is provided in English (Supplementary Data Sheet 2) and German language (Supplementary Data Sheet 3).

#### 2.4.2 Standard physiotherapy (control group, CG)

Standard physiotherapy (CG) includes conventional post-stroke rehabilitation exercises. Exercise types were evaluated using a questionnaire for the pilot trial (Meier et al., 2021), confirmed for this RCT in the three study centers and corresponding with standard physiotherapy according to guidelines for stroke rehabilitation (Winstein et al., 2016; Intercollegiate Stroke Working Party, 2023). Exercises in CG can be categorized into four different groups:

Trunk stability training: strengthening and segmental stabilization (Figure 2).Training activities of daily living (ADL): dressing, washing, changing body position (e.g., lie-to-sit, sit-to-stand) with and without aids.Walking training: walking with assistance or with an assistive device, variation of step length/step width/walking speed, stair climbing, walking on uneven ground.Balance training: using balance pads, exercises for shifting the body center of gravity, exercises with reduced support-surface.

**Figure 2 F2:**
[figure not shown]
Control group exercise example.

The central principle of the CG is to keep goals and exercises in therapy relevant to everyday life. Therefore, the exercises are designed to target specific activities involving intricate movements such as transitioning from lying to standing, dressing oneself, or preparing a cup of coffee. While each repetition may take longer compared to the IG due to the complex sequence of activities involved, the exercises should still strive for a high number of repetitions in line with general stroke rehabilitation guidelines. The repetition count may vary depending on factors such as task duration, allowing for variability within the therapy session to cater to the patient's performance levels. This variability aims to maintain a level of challenge and interest for the patient. Additionally, considering the patient's condition is crucial; for instance, acute stroke patients may experience dizziness with repeated changes in body positions. Similar to the IG, exercise difficulty is adapted to the patient's limit of performance, but patients in the CG can receive support from the therapist or an assistive device to be able to perform the exercise. Another aspect in this group is to emphasize balance training, stability training and strengthening of the trunk.

Further information about the exercises in this group are reported using the TIDieR (Supplementary Data Sheet 4). The exercise handout for the CG is provided in English (Supplementary Data Sheet 5) and German language (Supplementary Data Sheet 6).

#### 2.4.3 Home exercise program

In addition to the supervised practice, patients in both groups are asked to practice independently 5 times per week, for 15 min throughout the 4-week intervention period (total 20x). The exercises for each day are provided during the supervised sessions according to their group assignment and level of performance.

Upon completing supervised treatments, both IG and CG patients are given a personalized home exercise program as a handout. This program includes a variety of exercises, tailored to each patient. Patients have the flexibility to choose from these exercises for their independent practice, which is recommended 5 times per week, each session lasting 15 min, over an 8-week period until the last visit (T2 assessment), totaling 40 sessions (Table 1). If IG patients have safely practiced with trampolines during supervised treatment, they are provided with a trampoline for continued exercise performance.

#### 2.4.4 Similarities and differences of the interventions

Both interventions follow the principles of motor learning; however, there are distinct differences between them. In the IG, exercises typically involve more repetitions but less variability in practice due to the exercise nature. Conversely, in the CG, there is more practice variability with fewer repetitions. The IG emphasizes allowing the body to sway and solving fixation mechanisms, which is not a central focus in the CG. Patients in the CG concentrate on enhancing stability through trunk exercises while in the IG, this aspect is not as prominent. The CG places a stronger emphasis on training for activities of daily living compared to the IG. Both interventions include walking training, but the approach differs. In the CG, walking training is scheduled regularly regardless of support levels, whereas in the IG, gait training is preferred at times when it can be executed without fixation mechanisms, therapist assistance, and with a focus on coordination.

#### 2.4.5 Strategies to improve adherence to interventions

To document independent practice sessions and facilitate adherence, patients are provided with a checklist. To enhance adherence further, patients undergo semi-structured phone call interviews every 2 weeks. These interviews encompass questions on the exercise frequency, experience and any issues encountered during the exercises, including aspects such as the exercise environment and motivation. Additionally, the interviews cover questions regarding completion of adherence and falling checklist (Table 2).

**Table 2 T2:** Semi-structured telephone interview questions.

	**Question**	**Prompts**
1.	Please indicate how often you practice per week?	If not 5 times per week: What prevents you from practicing 5 times per week?
2.	Please indicate for how long you practice per day?	If not 15 minutes per day: What prevents you from practicing 15 min per day?
3.	Please describe how you get along with the exercises.	If there are problems: Could you provide explanations for this?
4.	Are you using the compliance checklist for documentation?	If not: Could you provide explanations for this?
5.	Are you using the fall protocol?	If not: Could you provide explanations for this?

#### 2.4.6 Relevant concomitant care

While a multi-disciplinary rehabilitation regimen may encompass speech therapy and occupational therapy, these are only included if deemed necessary for the patient. There are no additional one-on-one physiotherapy sessions beyond the trial intervention. Other rehabilitation modalities offered in the rehabilitation facilities may involve robotic interventions or group therapies with an exercise therapy focus (endurance training, strength training, Nordic walking, etc.) or an occupational therapy focus (crafting, gardening, writing training, etc.). The selection of additional therapies for study participants may vary based on individual patient needs, to deliver tailored care.

### 2.5 Data collection

Data is collected at the baseline (T0 assessment), after the 4-week phase of supervised practice (T1 assessment) and after 3 months (T2 assessment; Table 1). T0 and T2 assessments take place at the Clinical Department of Neurology, Medical University of Innsbruck, Austria. T1 assessment is conducted in the patients' rehabilitation facility. Demographic data (age, sex) and stroke-specific data (location, type, lesion side, and timepoint) are extracted from medical records. Outcomes of balance, walking, ataxia, and fear of falling are obtained from trained assessors.

Personal data is pseudonymized using a patient identification number (ID) and only pseudonymized data is transferred to statistical analyses. To ensure the plausibility and integrity of the data, random data checks (value range, field type, and logic checks) are performed, and the CRF data is entered into the database by two independent researchers.

#### 2.5.1 Primary outcome

The primary outcome is balance as assessed using the BBS (Berg et al., 1989). The BBS is considered the gold standard for evaluating balance in people after stroke (Blum and Korner-Bitensky, 2008). It comprises 14 items, and a Likert scale is used ranging from 0 to 4, depending on the patient's performance (Table 3).

**Table 3 T3:** Outcomes, assessments, and timepoints.

**Outcome**	**Assessment**	**T0^a^**	**T1^b^**	**T2^c^**
**Primary outcome**		
Balance	Berg Balance Scale (BBS)	x	x	x
**Secondary outcomes**		
Severity of ataxic symptoms	Scale for the Assessment and Rating of Ataxia (SARA)	x	x	x
Balance	Posturography using the TYMO^®^	x	x	x
Balance (trunk control)	Trunk Control Test (TCT)	x	x	x
Balance	Functional Gait Assessment (FGA)		x	x
Risk of falling	Functional Reach Test (FRT)	x	x	x
Concerns about falling	Falls Efficacy Scale International (FES-I)	x	x	x
Number of falls	Structured log		x	x
Walking	Functional Ambulation Categories (FAC)	x	x	x
Walking	Timed Up and Go (TUG)	x	x	x
Quality of life	EuroQol five dimensions questionnaire (EQ-5D-3L)		x	x
Independence in daily life	Scores of Independence for Neurologic and Geriatric Rehabilitation (SINGER)		x	x

^a^Assessment at baseline.

^b^Assessment after 4-week intervention.

^c^Assessment after 8 weeks of home exercise.

#### 2.5.2 Secondary outcomes

Secondary outcomes are static balance, as assessed using posturography (Tymo Balance Plate, Tyromotion, Austria), dynamic balance during walking, measured using the Functional Gait Assessment (FGA; Thieme et al., 2009), and trunk control, as assessed using the Trunk Control Test (TCT; Collin and Wade, 1990). Additionally, concerns about falling are assessed through the Falls Efficacy Scale International (FES-I; Yardley et al., 2005; Kempen et al., 2007), and risk of falling is determined according to the Functional Reach Test (FRT; Duncan et al., 1990, 1992). The number of falls is documented as well.

Further secondary outcomes include walking ability, evaluated using the Functional Ambulation Categories (FAC; Collen et al., 1990), functional mobility, as measured by the Timed Up and Go Test (TUG; Podsiadlo and Richardson, 1991), health-related quality of life, assessed utilizing the EuroQol questionnaire EQ-5D-3L (Rabin and de Charro, 2001; Greiner et al., 2005), severity of ataxic symptoms, as determined by the Scale for the Assessment and Rating of Ataxia (SARA), and patients' independence in daily life, measured using the Scores of Independence for Neurologic and Geriatric Rehabilitation (SINGER; Funke et al., 2009; Gerdes et al., 2012; Table 3).

Due to the time-point of study recruitment being a susceptible one for diminished physical and mental resilience (i.e., in the acute phase after stroke), FGA, EQ-5D-3L, and SINGER are not performed at T0.

Another secondary outcome for patients with cerebellar infarction is neuronal plasticity occurring over time, measured using magnetic resonance imaging (MRI) at T0 and T2. In addition to structural MRI, functional MRI is performed, including two motor paradigms: ankle dorsiflexion (Figure 3) and a balance task (Figure 4). As it is not possible to physically execute the balance task in the scanner, action observation plus motor imagery (AOMI) is performed while watching a video of a person doing the balance task. A combination of MI and video was chosen, as studies indicate a better activation of balance relevant brain areas than with MI or video alone (Taube et al., 2015; Ruffieux et al., 2018). MI capability is assessed using the Kinesthetic and Visual Imagery Questionnaire (KVIQ-10; Malouin et al., 2007). Mental chronometry, referring to the temporal coupling between real and simulated movement, is measured with a 6-Meter Walk Test (Lam et al., 2010). Assessments are validated to evaluate quality of MI (Schuster et al., 2012; Ma et al., 2022) and temporal consistency in stroke patients (Malouin et al., 2008; Malouin and Richards, 2010; Oostra et al., 2015; De Bartolo et al., 2020). After undergoing both assessments at T0, patients receive an MI training session before each MRI examination.

**Figure 3 F3:**
[figure not shown]
Functional magnetic resonance imaging paradigm—ankle dorsiflexion: the patient receives instruction about the upcoming task. The patient is asked to dorsiflex and plantarflex their foot in a constant, self-paced manner for 20 s, followed by a 20 s break. Visual stimulus presentation for stop (stop sign) and go (picture of a foot). Six cycles for each side.

**Figure 4 F4:**
[figure not shown]
Functional magnetic resonance imaging paradigm—balance task: the patient receives instructions about the upcoming task. The patient is asked to imagine themself balancing on a straight line while watching a video of a person walking on a line for 20 s, followed by a 20s break. Visual stimulus presentation for stop (fixation cross) and go (video of balancing task). Six cycles.

#### 2.5.3 Adverse event reporting and harms

Any adverse events (AE or serious AE) are recorded systematically, evaluated by authorized study personnel, and reported in accordance with responsible ethics committee requirements.

During the intervention phase (weeks 1–4), the occurrence of all adverse events is recorded by the responsible study center staff and assessed by a member of the medical team. The occurrence of falling during home exercises (weeks 5–12) is recorded by the patient as an adverse event of special interest, given that it serves as a secondary outcome within the study.

### 2.6 Sample size calculation

The sample size was estimated using the primary outcome data obtained from a pilot study (*n* = 7) conducted for this RCT (Meier et al., 2021), taking into account a correction for small samples. Based on a mean change in BBS score of 17.33 points (SD 2.08) in the IG and 13.67 points (SD 4.73) in the CG, the mean between-group difference and pooled SD were calculated and a correction for small samples was applied (pooled SD^*^1.442; Vickers, 2003). Using an independent samples *t*-test, power of 0.8, alpha of 0.05 and 1:1 allocation ratio, a sample size of 66 participants, 33 per group, was evaluated (HyLown Consulting LLC, 2022). Considering an attrition rate of 15%, the aim is to include 77 participants.

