### 2.7 Statistical analysis

IBM SPSS software, release 29.0 (IBM Corporation, Armonk, New York, USA), R software version 4.3.2 (R Foundation for Statistical Computing, Vienna, Austria) and GraphPad Prism 10 (San Diego, California, USA) will be used for the data analyses. Descriptive statistics are used for the baseline demographic variables, primary and secondary outcomes. Continuous data is checked for significant outliers using studentized residuals and a normal distribution using the Shapiro Wilk Test, Q-Q plots, and histograms. Frequencies [number (N), %] are presented for counted (N falls, N adverse events if any, N of home exercises) and nominal data (gender, stroke etiology and location, and rehabilitation facility). Medians (interquartile range) are reported for ordinal data (mRS, BBS, FGA, TCT, FES-I, FRT, EQ-5D-3L, SARA, and SINGER), and mean (SD) is reported for continuous data (age, time after stroke, TUG, and posturography outcomes).

The significance level is defined by a two-tailed *p*-value of <0.05. Baseline (T0) between-group differences are evaluated using Fisher's exact test for nominal data, Mann Whitney-*U*-test for ordinal data and independent samples *t*-test for continuous data. If the distribution is non-normal in continuous data, data transformation or non-parametric statistics are performed, as appropriate. To evaluate within-group differences between T0, T1, and T2 measures, for ordinal data, Friedman test is utilized followed by Dunn's multiple comparisons test for pairwise comparisons. To examine between-group differences, using newly created variables (T1 or T2 minus T0 values), a Mann Whitney-*U*-test is performed. For continuous data, test assumptions for a repeated-measures analysis of variance (ANOVA) are checked (e.g., normality, sphericity) and dealt with as appropriate. If the requirements are met, repeated measures ANOVA are performed, with “time” (T0, T1, and T2 measurements) as the within-subject factor, “group” (IG, CG) as the between-subject factor, and adjusted for the stratification variables (age, sex). If statistical significance is present, a *post-hoc* analysis of pairwise comparisons between measurement time points is performed, followed by a *post-hoc* Bonferroni correction for multiple comparisons. An intention-to-treat analysis is performed analyzing all study participants in the groups which they have been assigned to.

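### The stated 0.8 power belongs to a t-test, but the Berg Balance Scale will be compared by Mann-Whitney, with power about 0.77 if changes are normal

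*Protocol article*

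**What the plan says.** Section 2.6 of the protocol article takes its inputs from "primary outcome data obtained from a pilot study (*n* = 7) conducted for this RCT". These are a "mean change in BBS score of 17.33 points (SD 2.08) in the IG and 13.67 points (SD 4.73) in the CG", after which "a correction for small samples was applied (pooled SD^*^1.442" to the SD. The test is named: "Using an independent samples *t*-test". The result is given as "power of 0.8, alpha of 0.05 and 1:1 allocation ratio, a sample size of 66 participants, 33 per group, was evaluated", and the allowance for loss follows: "Considering an attrition rate of 15%, the aim is to include 77 participants".

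Section 2.5.1 makes the BBS the primary outcome. Section 2.7 places it among the ordinal measures: "Medians (interquartile range) are reported for ordinal data (mRS, BBS, FGA, TCT, FES-I, FRT, EQ-5D-3L, SARA, and SINGER". For ordinal outcomes, that section compares the groups with a Mann-Whitney U test on the change from T0 to T1 or to T2. The t-test (at baseline) and the repeated-measures ANOVA are assigned to continuous data. Testing is two-sided: "The significance level is defined by a two-tailed *p*-value of <0.05". The Discussion says that the main interest is the change from T0 to T1.

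**The concern.** The trial is sized for one test and its primary outcome is analysed with another. Sections 2.6 and 2.7 both state their test outright, so this is not a detail left to a document that is not shown. When changes are normally distributed, Mann-Whitney is slightly less efficient than the t-test, so 0.8 overstates the power of the planned comparison. If the trial is neutral, readers will judge that result against a power figure that was worked out for a different test.

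Two smaller features of the same paragraph push in the same direction: how 33 was reached, and how 77 was rounded.

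**Working it through.** **Inputs (section 2.6; two-sided testing from section 2.7).** Mean changes 17.33 and 13.67; SDs 2.08 and 4.73; SD factor 1.442; alpha 0.05; power 0.80; 1:1 allocation; attrition 15%.

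**Step 1: reproduce the stated size.**
- Difference: 17.33 − 13.67 = 3.66.
- Pooled SD, equal weights: √[(2.08² + 4.73²)/2] = 3.654. Inflated: 3.654 × 1.442 = 5.269.
- Standardised effect: 3.66/5.269 = 0.695.
- Normal approximation: n = 2(1.960 + 0.842)²/0.6947² = 32.53, so 33 per group and 66 in total. This matches the plan.

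The article does not state the equal weighting. I infer it because it returns 33, whereas weighting by a 3/4 or 4/3 split of the seven pilot patients gives 37 or 29 per group.

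**Step 2: the test named in section 2.6.** With the noncentral t distribution the requirement is 33.52, so 34 per group. Power at 33 per group is 0.794.

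**Step 3: attrition.** 66/0.85 = 77.65, which rounds up to 78. In the other direction, 77 × 0.85 = 65.45, so 65 analysable patients (33 and 32). Exact t-test power at 33/32 is 0.787.

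**Step 4: the test planned in section 2.7.** The difference is 3.66, the SD is 5.269 in both arms and changes are normal. The efficiency of Mann-Whitney relative to the t-test is then 3/π = 0.955. The simulations used 40,000 runs per setting.

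| Analysed | t-test, exact | Mann-Whitney, by 3/π | Mann-Whitney, simulated |
|---|---|---|---|
| 33 + 33 | 0.794 | 0.775 | 0.771 |
| 33 + 32 | 0.787 | 0.768 | 0.765 |

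By the 3/π method, Mann-Whitney power is 0.799 at 35 per group and 0.810 at 36. A calculation aimed at 0.80 would therefore have given about 36 per group, or 72 analysed. At 15% attrition that is 72/0.85 = 84.7, so 85 enrolled.

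**Step 5: dependence on distribution.** The article does not give the shape of the changes.
- If each arm keeps its own SD (each × 1.442), simulated Mann-Whitney power is 0.759 at 33 per group.
- At the lower bound of relative efficiency for a shift between two distributions of the same shape (0.864), power at 33 per group is 0.731.
- With heavier tails and the same difference and SD, simulated power at 33/32 is about 0.85 (t with 5 degrees of freedom) and 0.89 (Laplace).

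**The case against.** The strongest reply is that the stated size follows from its inputs, and this is correct. A reader might infer from the three discrepancies that the sample size is wrong or the trial underpowered. The documents do not support that. The normal approximation costs one patient per group, and 0.794 rounds to the one-decimal figure in the text. The attrition rounding costs one enrolled patient against a planning rate of 15%. Both are rounding matters.

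The other replies limit the size of the point but do not remove it:

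- **Shape.** The loss depends on normal changes with similar SDs, and heavier tails would favour Mann-Whitney. So 0.77 is a conditional figure. The Discussion does warn of a possible BBS ceiling, so a favourable shape cannot be taken for granted.
- **Planning uncertainty.** The inputs come from seven pilot patients and the SD is already inflated by 44%. The move from 29 to 37 per group under other pooling weights is larger than the gap at issue. This bears on severity; the stated power still refers to a different test.
- **Analysable number.** The 15% is not tied to a visit, and section 2.7 specifies intention to treat. If 72 of 77 patients had T1 data (5/77 = 6.5% loss), Mann-Whitney power would be about 0.81 by the 3/π method. Having 65 analysable patients at T1 is therefore an assumption.

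**Conclusion.** The point stands as a mismatch between the sizing test and the primary analysis test, and it is minor. On the plan's own difference and inflated SD, with normal changes and equal SDs, the planned Mann-Whitney comparison has power of about 0.77 at 33 per group. If the full 15% attrition applies at the primary time point, it is 0.76 to 0.77. Against the stated 0.8, that is a loss of roughly 2 to 4 points. It rests on equal-weight pooling, which is inferred, and on a distribution that the article does not give, so true power could be lower or higher.

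The figure of 85 enrolled in the working only measures the gap. It should not be read as a call to recruit more patients. The normal-approximation and attrition points are accurate, but they are not errors of consequence in the stated power or enrolment.

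**What to change.** Either of two changes settles it.

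1. Restate the power in section 2.6 for the planned test. For example: with 77 enrolled and 15% attrition assumed at the primary time point (65 analysable), power is about 0.77 for the Mann-Whitney test if BBS changes are normal with equal SDs, and may be higher or lower otherwise.
2. Make the sizing test and the primary analysis test the same, and fix that choice before unblinding, which section 2.3.3 places after study completion. If a baseline-adjusted model were chosen, its power would depend on the correlation between baseline and follow-up. The article does not give that correlation, so no gain should be claimed without stating an assumed value.

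In the same edit, say that 33 per group comes from a normal approximation (exact t-test power 0.794), and give 78 as the result of 66/0.85. The cost is a few sentences and a slightly less favourable power statement. No further enrolment is needed.
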